**Fig. 2 Fig2:**
[figure not shown]
Overview of the test procedure. Timepoints of Measurement. OXT = oxytocin, CORT = cortisol, TSST = Trier Social Stress Test, VAS = Visual Analogue Scale, min = minutes

### Power calculation

An a-priori power calculation was conducted using G*Power 3 [65] assuming a level of significance of *p *< 0.05, an effect size of f = 0.4 and two groups. The effect size of f = 0.4 was based on the study published by Bernhard et al. [32] and determined from the effect of TSST on CORT and OXT. The power analysis—when considering a correlation between CORT and OXT (as found by Bernhard et al. [32])—was conducted for a rmMANOVA (repeated measures Multivariate Analysis of Variance) and considered 8 measurements of CORT and OXT. Here, a sample size of 30 was estimated to achieve sufficient power of 80%. In case of no correlation between CORT and OXT, an rmANOVA (repeated measures Analysis of Variance) will be performed. Power analysis revealed that here a sample size of 8 will be required to achieve sufficient power of 80%. To determine the effects of group and sex on basal OXT and OXT increase through an additional MANOVA, a power analysis with an estimated effect size of f = 0.25 (medium sized effect) determined a total sample size of 64 (32 participants in each group). The latter sample size was chosen.

### Statistical analysis

To ensure objectivity the data will be assessed in accordance with the current standards of empirical research. The collected data will be evaluated using SPSS 25.0 (IBM Corp. Released 2017. IBM SPSS Statistics for Windows, Version 25.0. Armonk, NY: IBM Corp.). Using $$x^{2}$$—test for discrete analysis of variance (ANOVA) for continuous variables with group and gender as inter-subject factors, the demographic and psychometric data will be evaluated. The measured OXT and CORT levels will be transformed to achieve normal distribution. Correlations between psychological VAS ratings and OXT and CORT will be explored through Pearson correlations in case of normally distributed data and through Kendall’s τ otherwise. As correlation between OXT and CORT is expected, a rmMANOVA (repeated measures Multivariate Analysis of Variance) will be conducted to test the effects of time as a within-subject factor and group as a between-subject factor on OXT and CORT reactivity. In case of correlation between OXT, CORT and VAS ratings, VAS ratings will be included into the rmMANOVA, otherwise separate ANOVAs with the between-subject factor group and within-subject factor time will be conducted. In case of significant main effects or interactions, False Discovery Rate (FDR) [66] corrected post-hoc tests will be performed. Exploratory post-hoc analyses with FDR corrected p-values testing for effects of sex and age on OXT and CORT reactivity will also be conducted.

OXT and CORT increase will be calculated through area under the curve (AUC) analyses as described in Pruessner et al. [67]. Additionally, delta scores will be computed between the OXT and CORT baseline measure and the highest value for a measure of increase [68, 69] and between the highest OXT and CORT value and the lowest value after stress for a measure of recovery [70]. To determine group differences between OXT and CORT baseline, increase and recovery, MANOVAs will be computed with group as a between-subject factor and sex as a within-subject factor. In exploratory analyses, anxiety and depressive symptomatology scores will be included as covariates. As previous research has identified an effect of contraceptives on OXT baseline levels [38] a separate analysis will be run on female participants.

To assess the relationship between OXT and CORT reactivity, FDR-corrected correlations will be computed between CORT and OXT baseline levels and the increase and recovery measures. In case of significant correlations between CORT and OXT, a linear multiple regression model will be computed with CORT increase as dependent variable and OXT increase, CORT baseline and group as predictors to determine the amount of variance that is explained by OXT increase independently of baseline CORT. An additional regression model will be computed with CORT recovery as dependent variable and OXT increase and CORT increase as predictors. Effect sizes will be reported using Cohen’s *d* with 0.2 being considered a small, 0.5 a medium and 0.8 a large effect.

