In the study by Bernhard et al. [32], the salivary cortisol (CORT) concentration was examined as a second neurophysiological parameter of stress reaction. The adrenal cortical hormone CORT is an elementary component of the hypothalamic–pituitary–adrenal (HPA) axis and the endocrinological stress regulation system. A meta-analysis by Cardoso et al. [34] supported the hypothesis that OXT plays an important role in the etiology of HPA dysfunction associated with psychopathology. The detailed interplay of OXT and CORT under stress conditions has rarely been studied [32]. In a human study in 2003, Heinrichs et al. [35] were the first to observe that the combination of i.n. OXT and social support suppressed CORT levels under stress conditions (TSST) and resulted in increased calmness and decreased anxiety. In healthy participants i.n. OXT, as well as natural high baseline OXT concentrations in saliva, appear to be correlated with low CORT response and less anxiety in stressful situations [32, 35, 36]. In contrast, lower baseline OXT was associated with higher CORT levels and greater OXT reactivity [32]. To the best of our knowledge, the only study addressing this relationship in children and adolescents was conducted by Bernhard et al. [32]. In the study, healthy children and adolescents showed an earlier peak of salivary OXT at + 1 min after stress compared to the CORT level at + 10 min after stress. Furthermore, they showed an earlier decrease of OXT to the baseline level compared to CORT after stress exposure was terminated [32]. Based on the earlier OXT peak, the authors assumed that OXT has a regulatory effect on CORT, which may act as a support mechanism during stressful situations [32]. In the present study, we expect a dysregulated interplay between OXT and CORT under stress [34] in children and adolescents suffering from anxiety disorder compared to healthy controls. If children and adolescents with anxiety disorder show a low basal OXT level (see above), there are two possible assumptions on the interplay between OXT and CORT. On the one hand, since low basal OXT levels in healthy participants correlated with a higher increase of saliva OXT and CORT during the TSST [32], we expect participants with anxiety disorder to show less increase of OXT, thereby reflecting a pathological lacking stress-buffering mechanism [15] and a subsequently higher expression of subjective stress and anxiety [35, 37]. On the other hand, because of the HPA axis co-activation and greater stress-induced OXT reactivity associated with faster vagal recovery, Engert et al. [38] rather suggested a “recovery-boosting” than a “reactivity-buffering” effect. With respect to previous research, however, the influence of OXT on the HPA axis under stress has not been fully determined yet, especially regarding clinical populations. Recent findings describe a blunted CORT response to psychosocial stress (TSST) in women with anxiety disorder [39] and patients with panic disorder [40, 41]. These findings led to the hypothesis of a HPA-axis hypo-responsiveness in patients with mental health disorders, promoting high vulnerability during acute stress response. This was also found in studies with adolescents with non-suicidal self-injury (NSSI) [42].

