### Primary hypothesis

It is hypothesized, that the endogenous OXT system of children and adolescents (11–18 years of age) suffering from a clinically diagnosed anxiety disorder is dysregulated. As different types of anxiety disorders in children have been associated with dysregulation of the HPA-axis [43], no differences between different types of anxiety disorders in response to stress are expected. A lower basal OXT level of the experimental group, as well as less OXT release as a response to an acute stressor, is expected, compared to the control group. In both groups, it is assumed that the OXT level peaks and decreases earlier than the CORT level. We expect a negative correlation between basal OXT level and CORT increase in both groups. Basal OXT and OXT increase under stress are expected to correlate positively with subjective stress level (VAS). OXT increase is expected to correlate positively with vagal recovery. In healthy controls, we anticipate a positive correlation between OXT release and CORT release. As described in the background section, in participants with anxiety disorders two controversial hypotheses about the interplay between CORT and OXT under stress will be discussed. First, participants with anxiety disorders might show low OXT increase correlating with high CORT increase reflecting a pathological, lacking stress-buffering effect of OXT. Second, participants with anxiety disorders might show low OXT increase correlating with attenuated CORT response reflecting HPA-axis hypo-responsiveness.

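### The hormone–VAS and OXT–CORT correlations carry no group term, so on their plain reading they mix the patient–control mean difference with the within-group association

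*Protocol article*

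**What the plan says.** In the protocol article, Statistical analysis, two sets of correlations are planned.

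- Hormones with subjective ratings: "Correlations between psychological VAS ratings and OXT and CORT will be explored through Pearson correlations in case of normally distributed data", with Kendall's τ otherwise. The result also selects the model. If OXT, CORT and VAS correlate, VAS joins the rmMANOVA; if not, VAS is analysed in separate ANOVAs.
- OXT with CORT: "FDR-corrected correlations will be computed between CORT and OXT baseline levels and the increase and recovery measures". If these are significant, a regression of CORT increase follows with OXT increase, CORT baseline and group as predictors. A second regression, of CORT recovery, lists OXT increase and CORT increase but not group.

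The Primary hypothesis section states the OXT–CORT predictions by group: "We expect a negative correlation between basal OXT level and CORT increase in both groups" and "In healthy controls, we anticipate a positive correlation between OXT release and CORT release". For patients it offers two competing hypotheses: a small OXT increase going with a high CORT increase, or with an attenuated one. The OXT–VAS prediction is positive, for both basal OXT and OXT increase, and names no group.

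The same section expects the groups to differ in mean OXT: "A lower basal OXT level of the experimental group, as well as less OXT release as a response to an acute stressor, is expected". In the Background, one of two alternatives gives patients a "subsequently higher expression of subjective stress and anxiety". The Objectives make the group difference in the CORT–OXT relation the third main question.

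**The concern.** The Statistical analysis section names group where it uses it: in the demographic ANOVAs, the rmMANOVA, the MANOVAs and the CORT-increase regression. It also announces its one subgroup run, in females. The correlations have neither a group term nor a split, and each set acts as a single yes/no condition for what follows. Carried out literally, that gives one coefficient over patients and controls together.

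Such a coefficient has two parts: the association between individuals inside each group, and a part due only to the difference in group means. If patients are lower on OXT and higher on VAS, the second part is negative whatever happens inside the groups. The pooled test can then reject with no within-group association, or miss a positive one. For OXT and CORT, a single coefficient also cannot show the differing patterns that the hypotheses allow in controls and patients. If it is not significant, the CORT-increase regression may never be run.

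**Working it through.** **Inputs.** From the Power calculation section: 32 per group, 64 in total, and a significance level of 0.05 (sidedness is not stated; two-sided is assumed here). The protocol gives no figure for any correlation, so there is none to reproduce. It also gives no group shift for these variables. The OXT shift is assumed to be d = −0.5 to −0.8; the lower end matches the generic f = 0.25 of the power calculation, since d = 2f for two equal groups. The VAS shift is assumed to be d = +0.5 to +1.2.

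**Formula.** For two equal groups with common within-group SDs, and mean differences dx and dy in SD units:

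r_pooled = (r_within + 0.25·dx·dy) / √[(1 + 0.25·dx²)(1 + 0.25·dy²)]

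Rejection rates use Fisher's z. The pooled test has z = atanh(r_pooled)·√61. Two groups of 32 combined have information 29 + 29 = 58.

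**Worked case, −0.5/+0.8.** With r_within = 0: −0.10 / √(1.0625 × 1.16) = −0.10/1.110 = −0.09. Then |z| = 0.0903 × 7.81 = 0.71 and the rejection rate is 11%. With r_within = +0.30: 0.20/1.110 = +0.18.

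| OXT / VAS shift | pooled r if within = 0 | false positives | pooled r if within = +0.30 | pooled power |
|---|---|---|---|---|
| −0.5 / +0.5 | −0.06 | 8% | +0.22 | 43% |
| −0.5 / +0.8 | −0.09 | 11% | +0.18 | 30% |
| −0.8 / +0.8 | −0.14 | 19% | +0.12 | 16% |
| −0.8 / +1.2 | −0.19 | 33% | +0.05 | 7% |

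Combining the two within-group coefficients keeps the false-positive rate at 5%. For r = +0.30 its power is 65% (0.3095 × √58 = 2.36), whatever the group means are.

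**Simulation check.** In 10,000 simulated trials per scenario, the pooled Pearson test gave 8%, 11%, 20% and 34% false positives for the same four rows; the group-adjusted test stayed at 5%. With a true within-group r of +0.35, adjusted power was 81–82%, against 58%, 43%, 24% and 8% pooled.

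**Basal OXT and CORT increase.** Take r_within = −0.30 and OXT lower in patients by 0.5 or 0.8 SD.
- CORT increase higher in patients by the same amount: −0.3625/1.0625 = −0.34, and −0.46/1.16 = −0.40.
- CORT increase blunted by the same amount: −0.2375/1.0625 = −0.22, and −0.14/1.16 = −0.12.

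The first two values also show that a negative OXT–VAS association would be inflated.

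**Opposite slopes.** Correlations of +0.4 in controls and −0.4 in patients average to (0.4 − 0.4)/2 = 0, so with equal means the pooled r is 0.00. A group-adjusted coefficient averages to zero as well; only the group-specific coefficients show the pattern.

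**The case against.** The strongest reply is that pooling is inferred. The text never says that the groups are combined. The hypotheses point to a by-group reading, and a condensed article may leave such detail to the full plan. It stands that this is an inference. But the article does fix the coefficient types, the conditions that they trigger and the predictor lists, and it mentions group elsewhere in the same section. A by-group intention would also need a rule for when the two groups disagree, and none is given.

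Several other points stand in full:
- The CORT-increase regression does adjust for group, though only if the correlations are significant, and no group-by-OXT term is named.
- VAS responses are secondary, their correlations are exploratory, and VAS is tested for group and time whichever model is chosen.
- The VAS shifts are assumptions, and higher subjective stress in patients is one branch of a conditional argument. At 0.5/0.5 the false-positive rate is only 8%.
- The sign of the OXT–VAS association is unsettled in the article. The hypothesis is positive, but the Background reports that higher basal OXT went with less anxiety in healthy children.

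A reader might infer that the pooled correlations test the group mean difference and nothing else. They do not: the pooled r still contains the within-group r. A reader might also take the target to be a within-person association. Basal OXT is one value per person, so the quantity at risk is between people, within group.

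**Conclusion.** The concern holds in this form: as written, the correlations take no account of group, while the OXT–CORT predictions are stated by group. If the plan is carried out literally and the groups differ in the direction expected for OXT, with higher VAS in patients, false positives rise from 5% to about 8–34% and a within-group r of +0.30 appears as +0.22 to +0.05. These sizes rest on the assumed shifts, normal data, equal within-group SDs and a single two-sided test at 0.05. The FDR correction planned for the OXT–CORT set is not modelled. For basal OXT and CORT increase the direction of the bias is open, because the protocol leaves patients' cortisol response open.

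A reader might go further and expect the trial to report the wrong sign for a real positive association. That is not shown. At the largest shifts in the table, a true +0.35 pools to 0.11/1.256 = +0.09, and a significant negative result would occur about 0.4% of the time. The likelier harm is a missed association, or a spurious negative one when there is none within groups. Nor do opposite slopes necessarily prevent the regression: several correlations feed that condition, and the cancellation affects the OXT-increase with CORT-increase pair.

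**What to change.** In Statistical analysis, state that the hormone–VAS and the OXT–CORT baseline, increase and recovery correlations are computed adjusted for group (partial correlations, with values centred within group) and are also reported separately for patients and controls. Base the predictions in Primary hypothesis on these and not on a pooled coefficient.

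Name in advance which coefficient decides whether VAS enters the rmMANOVA and whether the CORT regression is run. For OXT–CORT this should include the group-specific coefficients, because an adjusted coefficient alone would still miss opposite slopes.

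The change is a few lines of text and needs no new data. Adjustment costs one degree of freedom. The group-specific estimates are less precise: with n = 32, power for r = 0.30 is 39%, and the smallest r detectable with 80% power is about 0.48, against about 0.35 for all 64. Adding group-specific coefficients also enlarges the set over which the FDR correction is applied.

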**Methods:**

The present study is a single-center experimental observation study to investigate the reactivity of the endocrinological system to a psychosocial stressor (TSST). 32 children and adolescents (11–18 years) suffering from anxiety disorder will be compared to a matched healthy control group. After a detailed psychological assessment, saliva samples will be taken to measure oxytocin levels before and after psychosocial stress exposure at eight different time points. Additionally, the stress hormone cortisol will be analyzed according to the same procedure.

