Upon completion of the TSST, participants will be seated in room A, thereby ending the stressful situation (T2c). To investigate the individual progression of coping with stress of each participant, no relaxing materials will be provided. Saliva samples will be taken at + 1, 5, 10, 20, 40 and 60 min after completing the tasks using Salivette^®^ (Sarstedt, Germany) collection devices and stored at − 20 °C until biochemical analysis. Salivary CORT will be measured at the laboratory of the Department of Biopsychology, Technical University of Dresden, Germany. Salivary OXT will be quantified by radioimmunoassay (RIAgnosis, Sinzing, Germany). In order to monitor the stress reaction during the procedure, heart rate will be recorded by an Ecg Sensor (EcgMove4, movisens, Germany) fixed with adhesive electrodes at the chest of each participant. Simultaneously to the physiological assessments, subjective levels of perceived stress, anxiety, insecurity and tension will be investigated using the Visual Analogue Scale (VAS) (Scale from 0 = feeling not stressed/anxious/insecure/tense at all to 100 = feeling highly stressed/anxious/insecure/tense, for more details see Hellhammer and Schubert, 2012 [37]) at 9 different time points [32]. In the relaxation period after the TSST, the experimenter will provide participants with positive feedback on their performance and the information that no video recording was made [32]. Finally, a clinical psychologist or doctor in charge will be available to talk in detail with the study participants and their legal guardians about the test procedure. He will also be available for advice/counseling if needed. See Fig. 2 for an overview of the test procedure.

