### Safety report

All participants will be informed in advance where to seek help for mental health problems during the procedure and that they can withdraw their consent for participating at any time. Because communication with strangers could induce increased stress levels, especially for anxious patients, participants may feel overburdened and symptoms of anxiety may be intensified during the stress test. If patients are unable to calm down through positive encouragement, the study will be terminated.

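### The model that tests the oxytocin response is chosen from observed correlations without a criterion, and its version with VAS ratings mixes 8- and 9-point series

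*Protocol article*

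**What the plan says.** The Objectives make the salivary OXT response to the TSST, patients against controls, the second of three main questions. Perceived stress, anxiety, insecurity and tension (the four VAS scales) are secondary.

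Statistical analysis plans an rmMANOVA of OXT and CORT with time and group as factors, because the two hormones are expected to correlate. It then adds a rule for VAS: "In case of correlation between OXT, CORT and VAS ratings, VAS ratings will be included into the rmMANOVA, otherwise separate ANOVAs" are run. FDR-corrected post-hoc tests follow only if a main effect or interaction is significant. Power calculation has a second switch: "In case of no correlation between CORT and OXT, an rmANOVA (repeated measures Analysis of Variance) will be performed".

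The same section computes OXT and CORT increase by AUC and by delta scores, and compares baseline, increase and recovery between groups by MANOVA.

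On timing, the Abstract says that saliva is taken "before and after psychosocial stress exposure at eight different time points". The section on physiological measures accounts for these: one home sample, one at 1 minute before the TSST and six afterwards. It collects VAS "at 9 different time points", while describing the ratings as simultaneous with the physiological assessments. The repeated-measures power calculation "considered 8 measurements of CORT and OXT" and does not mention VAS.

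**The concern.** A primary question should have one test that can be named before the data are seen. Here there are three candidates (OXT alone, OXT with CORT, OXT with CORT and VAS), and the rule that picks among them is incomplete. Even if only same-time OXT–CORT coefficients are considered, there are 8 of them, or 16 if taken by group. Two careful analysts could run different primary tests on the same data.

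The joint versions also answer a different question. A significant group-by-time result for OXT, CORT and VAS together may come wholly from perceived stress. A non-significant one closes the route to the OXT post-hoc tests even when OXT differs. Finally, a 9-level and an 8-level series cannot share one within-subject time factor unless the plan says which points are matched.

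**Working it through.** **1. The plan's own figures.** Inputs from Power calculation: α = 0.05, f = 0.4, two groups, m = 8 measurements. The article does not give the correlation among repeated measures; ρ = 0.5 is assumed.
- N = 30 (rmMANOVA): λ = f²·N·m / (1 + (m − 1)ρ) = 0.16 × 30 × 8 / 4.5 = 8.53. With df 1 and 28 the power is 0.805. The figure reproduces, as a test of the group main effect.
- N = 8 (rmANOVA): λ = f²·N·m / (1 − ρ) = 0.16 × 8 × 8 / 0.5 = 20.48. With df 7 and 42 the power is 0.88. The figure reproduces, as a time or group-by-time effect.

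Neither calculation contains VAS. The chosen N = 64 comes from the additional MANOVA on basal OXT and OXT increase.

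**2. Power for an effect that lies in OXT only.** Two-group Hotelling test of group-by-time at N = 64, with p = 7 × number of outcomes (8 time points give 7 contrasts; VAS is taken at 8 points for this purpose) and df p and 64 − p − 1. For OXT alone, p = 7 and df2 = 56; power of 80% needs λ = 16.22. That signal is held fixed. If the added outcomes carry no group effect and have correlation r with OXT (jointly, where several are added), λ becomes 16.22 / (1 − r²).

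| Model | p | df2 | r = 0 | r = 0.3 | r = 0.5 | r = 0.6 | r = 0.7 | r = 0.8 |
|---|---|---|---|---|---|---|---|---|
| OXT + CORT | 14 | 49 | 61% | 67% | 77% | 85% | 93% | 99% |
| OXT + CORT + 4 VAS | 42 | 21 | 20% | 22% | 27% | 32% | 41% | 59% |

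Break-even with OXT alone: OXT + CORT needs λ = 22.9 for 80%, so r = √(1 − 16.22/22.9) = 0.54. With all four VAS scales it needs λ = 65.9, so r = √(1 − 16.22/65.9) = 0.87. With one VAS scale added to the hormones (p = 21, df2 = 42), power at r = 0 is 47%.

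**3. Type I error of the switch.** In a simulation of choosing between the OXT-only and the OXT + CORT test from the observed correlation, the rejection rate of the selected test under the null was 4.7% to 5.7%. No inflation was shown.

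**4. Time points.** Hormones: 1 + 1 + 6 = 8. VAS: 9. At least one VAS occasion has no hormone value, and the text does not say which.

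**5. Complete cases, as an illustration.** A standard rmMANOVA uses participants with full data. Assume that each of the 8 sampling occasions is independently missing with probability q, and that a missed sample loses both hormones. Then 64 × (1 − q)⁸ participants remain: 59.1, 54.4 and 42.5 for q = 1%, 2% and 5%.

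**The case against.** - **Correlation is the condition for the joint model.** The zero-correlation figures therefore describe a case in which it would not be run. This stands for CORT: from r of about 0.54 upward, adding CORT raises power, so a general statement that the joint model dilutes power is not supported. For all four VAS scales the loss remains up to r of about 0.87. The article does not say that all four enter together.
- **The size depends on the form of the test.** Under sphericity, an averaged multivariate test gives about 67% (OXT + CORT) and 42% (plus four VAS) at zero correlation. The article does not say which form is meant.
- **The rmMANOVA is not the only test of OXT release.** The AUC/delta MANOVA also tests it and is unaffected by the switch. This is correct, but the article does not say which of the two answers the second question.
- **Post-hoc tests help to attribute an effect to OXT.** They do, but only after a significant joint result.
- **The time points may be matched in Figure 2, which is not shown here.** Restricting the model to shared points would also work. The text states neither.

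A reader might also infer that the switching inflates type I error (the simulation did not show this), or that one missing value certainly removes a participant (the article states no such rule, and missing-data handling may sit in an analysis plan not shown). A further tempting reading is that patients who stop early are lost and that this biases the contrast towards no difference. The Safety report says only: "If patients are unable to calm down through positive encouragement, the study will be terminated". It does not say that data already collected are discarded, and the article gives no basis for the direction of any OXT bias. Its hypothesis expects less OXT release in patients, while its background links low basal OXT in healthy youth to a larger rise.

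**Conclusion.** The point holds in this form: the article fixes badly how a main question is tested. The model depends on observed correlations with no stated criterion, secondary ratings can become co-dependent variables with OXT, the VAS version cannot be run on one time factor as written, and two routes to the OXT response stand side by side with neither named as primary. The harm is ambiguity about what counts as the result, and a joint test that may not concern OXT.

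The effect on power is conditional. With CORT added it ranges from a loss (61% at r = 0) through near parity (77% at r = 0.5) to a gain (85% at r = 0.6), against 80%. With all four VAS scales it is a marked loss, from 20% at r = 0 to 59% at r = 0.8. These figures assume a Hotelling-type test at N = 64, an effect in OXT only, and added outcomes without a group effect. The point should be corrected, but it does not invalidate the study.

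**What to change.** Delete both correlation-based switches and name one primary test of the second question. One suitable choice is a linear mixed model for transformed OXT alone, with group, time, group × time, sex and a within-person covariance, using all available samples; group × time is the test of interest. Analyse CORT and each VAS scale in separate supporting models, each on its own time points, so that the 8 and 9 points need not be forced together. Label the AUC/delta MANOVA as supporting. If the investigators prefer OXT AUC as the primary test, that also resolves the point, provided that it is named as the only one.

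The mixed model also keeps participants with an occasional missing sample, who would be lost under a complete-case analysis. The cost is a few sentences of analysis text, best dated before the hormone data are examined. The mixed-model procedure in SPSS is sufficient. Sample size, data collection and the safety rule do not change.
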